### Economic evaluation

The economic analysis will be performed from the societal perspective. The follow-up period is 12 months. Due to this short time frame, no discounting will take place. Cost-effectiveness ratios will be calculated by dividing the difference in average costs per patient between both intervention groups by the difference in primary outcome (time to complete re-epithelialization). Dressing changes are reported to be one of the most painful and traumatic aspects of burn treatment. This impact is not measured in the primary outcome measure (time to greater than 95 % re-epithelialization). In a sensitivity analysis, therefore, the difference in costs will be related to the difference in dressing changes between both treatments.

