### Study population

The study will be performed in two of the three burn centers (Beverwijk and Rotterdam) in The Netherlands. In these burn centers, both Flaminal® and Flamazine® are therapeutic options for treating partial thickness burns. Patients who are admitted to the Beverwijk or Rotterdam Burn Centre and who meet the following inclusion criteria will be eligible for this study: competent or temporarily non-competent (because of sedation and/or intubation); partial thickness burns of minimally 1 % total body surface area (TBSA) (possibly in combination with full thickness burns); hospital admission within 48 hours of burn injury; written informed consent by the patient. Patients meeting one or more of the following criteria are excluded: age below 18 years; TBSA of more than 30 %; burns caused by chemicals, electricity or radiation; if local therapy with a topical agent has already started; patients who are expected (according to the treating medical physician) to be non-compliant with the study protocol.

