### Recruitment, consent and randomization

All patients who are admitted to the burn center undergo standardized screening and baseline procedures according to the local protocol. The local investigator will check the inclusion and exclusion criteria of the study and will inform the participant about the study. If the participants are willing to participate in this study, they must provide written informed consent. If an eligible patient is temporarily non-competent because of sedation and/or intubation, a legal representative of the patient, according to the Dutch Medical Treatment Act (WGBO), will be informed about the study and will provide written informed consent. After the sedation or intubation has ended, the patient will be asked to confirm willingness to participate in the study in writing, otherwise the participation is discontinued and the collected study data will be destroyed.

After informed consent has been obtained, the largest partial thickness area will be assigned as the study area. Thereafter, the patient will be randomly assigned to one of the two study arms using TenALEA (Trans European Network for Clinical Trials Services), an online randomization program (www.flam-studie.nl). The online-randomization is stratified by center and uses variably sized blocks in a 1:1 ratio. In both participating hospitals the local trial coordinator will receive a username and password for online randomization. After randomization the local trial coordinator of that center and the central trial coordinator will receive an email with the inclusion number and the randomization outcome. The outcome will also be displayed on the website, only visible for the randomizing local and central trial coordinators. Then, all the burn wounds will be treated with the treatment that is assigned by the randomization.

When the study area that was initially assessed as a partial thickness burn, turns out to be a full thickness burn area after performing laser Doppler imaging (LDI), then the study area will be replaced: the second largest partial thickness area (confirmed by LDI) will then be chosen as the study area.

For practical reasons it is not possible to blind the patients. It is also impossible to blind the medical staff who provide the burn wound care, because they are involved in all aspects of the care and are able to recognize each treatment from its appearance. No blinding of other outcomes is also possible for the same reasons.

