### Outcome measures

#### Primary outcome

Primary endpoint is time to complete re-epithelialization (greater than 95 %) of the study area, in days, judged by two experienced burn specialists during each dressing change. Complete re-epithelialization of the study area is only affirmed when the two burn specialists agree with each other.

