#### Secondary outcomes/study parameters

o*Clinical outcomes:*Need for operation which is evaluated between 10 and 14 days post burn. Reasons for operation are that the experienced burn specialist expects no further wound healing in the next 7 to 11 days of the partial thickness area or a full thickness burn. If the decision to graft is made before 10 to 14 days post burn then the operation will still performed before 10^th^ day post burn day. The only indication for operation before the 10^th^ PBD is when a partial thickness burn becomes a full partial thickness burn. The treatment of full thickness burns is split skin graft in an early stagePercentage TBSA of the study area that covered with skin graftColonization: twice a week a wound swab will be taken from the study area. The wound swab will then be sent for laboratory investigation. In brief, the analysis of the wound swab will include the following steps. The microscopic examination will entail gram-staining. Thereafter, a quantity of the specimen will be cultured to obtain a pure single specimen culture. Finally, the sensitivity of the organisms to specific local therapy will be determined. In case of wound colonization the treatment will be changed to another relevant treatment based on the results of the wound cultureInfection: infection is suspected if a combination of skin redness, pain, swelling, tenderness, warmth, fever or pus draining from the wound is present. Infection is a clinical evaluation of the wound, in presence of absence of positive wound culture, and is judged by a physician at the burn center during each dressing changeNumber of dressing changesUse of systemic antibioticso*Patient-reported outcomes:*Pain will be measured during the application and removal of the wound dressing (procedural pain, measured directly after dressing change) and background pain (measured in the morning and evening). Pain will be measured twice daily during hospital admission by use of a Visual Analogue Thermometer (VAT), which is a numeric scale from 0 (no pain) to 10 (worst imaginable pain)Itching will be measured daily in the evening during hospital admission by use of a VAT [31]Anxiety: the Burn Specific Pain Anxiety Scale (BSPAS) will be scored on day 7 ± 2 post burn and on the day of discharge. The BSPAS is a valid and reliable nine-item self-report scale for the assessment of pain-related and anticipatory anxiety in burned patients [32, 33]Health-related quality of life (HRQoL) will be measured using the following questionnaires, in the week before discharge and at 3, 6 and 12 months post burn:Burn-specific quality of life (QoL) will be measured using the Dutch version of the Burn Specific Health Scale (BSHS)–Brief [34, 35]. The BSHS-Brief is a valid and reliable self-administered questionnaire that covers nine domains (heat sensitivity, affect, hand function, treatment regimens, work, sexuality, interpersonal relationships, simple abilities, and body image). The questionnaire takes 10–15 minutes to complete and 5 minutes to score. Responses are scored by the patient on a five-point scale from 0 (extreme) to 4 (none/not at all) for each of the 40 items. Mean scores are calculated for each of the domainsGeneral HRQoL will be measured using the EuroQol-5D (EQ-5D) questionnaire [36]. This simple and generic description of health status is widely used in studies on clinical and economic appraisal. The EQ-5D outcomes will be converted in utility scores between 0 (death) and 1 (perfect health) based on empirical valuations [37]. From the area under the utility curve during the 12 months of follow-up quality- adjusted life years (QALYs) will be calculatedo*Scar formation*: the following aspects of scar formation will be measured after 3, 6 and 12 months post burn:Scarring will be measured using the Patient and Observer Scar Assessment Score (POSAS), a valid and reliable scale that is designed for the evaluation of all types of scars by professionals and patients. It consists of two numeric scales: the Patient Scar Assessment Scale which is completed by the patient and the Observer Scar Assessment Scale which is completed by the medical staff. The variables scored by the patient are pain, itching, color, stiffness, thickness and irregularity [38–40]. The variables scored by the medical staff include vascularization, pigmentation, thickness, relief and pliabilityElasticity will be measured using a Cutometer (Courage & Khazak, Köln, Germany), a validated instrument to measure the vertical deformation of the skin in millimetres when the skin is pulled by means of a controlled vacuum into a circular aperture [41]Scar color and pigmentation will be measured using the DSM II colorimeter (Dermaspectrometer).This is a validated instrument to measure scar color by a narrow-band simple reflectance meter [41]o*Total (medical and non-medical) costs:* total costs in this study represent direct health care costs (inpatient and outpatient medical costs), direct non-healthcare costs and indirect non-health care costs (productivity loss). Personnel time and used materials for wound care and surgical procedures, hospital days for initial stay and re-admittance and outpatient visits during the first year will be measured prospectively as part of the case record form. Health resource use outside the hospital, travel costs and productivity losses will be recorded by questionnaires filled out by the patients at 3, 6 and 12 months post burn. Cost of dressing changes and surgical procedures will be assessed by translating the personnel time and used materials into costs by means of gross salaries and market prices. The costs of hospital stay and outpatient care in burn centers will be calculated by multiplying the number of hospital days respectively outpatient visits with their cost prices [42]. Other healthcare use will be translated into costs by standard prices [43]. Productivity losses will be valued using the friction cost method [44]o*Baseline parameters:* age, gender, skin type, wound etiology, bacterial contamination at admission, location of the wound, type of wound, TBSA% and co-morbidities. In all patients, the burn depth of the study area will be accurately determined on day 2–5 post burn by clinical evaluation and LDI scan using the moorLDI2-Burn Imager™ (Moor Instruments, Axminster, UK) and, based on pre-defined criteria (Table 1), be classified as superficial, intermediate or deep partial thickness injury. The size of each burn wound is then estimated in TBSA. In a LDI the low-intensity laser beam is scanned across a tissue surface in a raster fashion using a moving mirror. There is no direct contact with the tissue being assessed. The wounds are scanned by a trained research physician or nurse, after removal of topical medication (during regular wound treatment). All research physicians and nurses in both burn centers have followed the same training sessions and have the same experience. The scanning will take 1–5 minutes.

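### The cost-effectiveness ratio rests on an unadjusted difference in whole-patient costs; adjusting for burn size at admission would give the same unbiased target with better precision

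*Protocol article*

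**What the plan says.** All references are to the protocol article.

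- **Cost contrast.** Under Economic evaluation, the ratio comes from "dividing the difference in average costs per patient between both intervention groups" by the difference in time to re-epithelialization. No covariate is mentioned. The one sensitivity analysis replaces the denominator with the difference in dressing changes and leaves the cost contrast as it is.
- **Scope of cost.** Under Secondary outcomes/study parameters, the case record form captures "Personnel time and used materials for wound care and surgical procedures, hospital days for initial stay and re-admittance and outpatient visits during the first year". Patient questionnaires add care outside the hospital, travel and productivity loss. None of this is restricted to the study area.
- **Scope of treatment and effect.** Under Recruitment, consent and randomization, "all the burn wounds will be treated with the treatment that is assigned by the randomization". The effect measure concerns one area: "Primary endpoint is time to complete re-epithelialization (greater than 95 %) of the study area, in days".
- **Spread of burn size.** Study population requires at least 1% TBSA of partial thickness burn, allows full thickness burns alongside, and excludes TBSA above 30%.
- **Balance and covariates.** Randomization is 1:1, stratified by center only. Age and TBSA% are baseline parameters, and Table 2 places baseline parameters at admission.
- **Planned adjustment.** Statistical analysis plans a multivariable Cox model for the primary outcome only, and only if baseline looks unbalanced.

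**The concern.** A patient with a larger burn needs more dressing time and material, and coexisting full thickness burns bring surgery. With entry running from 1% to 30% TBSA and no stratification on size, the arms can differ by chance in mean burn size. In a plain difference of average costs that chance difference stays in the error term. TBSA% is collected but enters no planned cost model.

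Cost-effectiveness is in the trial's title and objective, yet Sample size calculation sets the number of patients for healing time alone. Recruitment closed on 20 October 2015, so precision for costs can no longer come from more patients. It can still come from the analysis.

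**Working it through.** **Inputs from the article.** 90 patients in total, taken as 45 per arm; TBSA limits of 1% and 30%. The article gives no cost SD, expected cost difference, TBSA SD or cost–TBSA correlation. It therefore has no cost figure to reproduce, and everything below that needs one of these quantities is conditional on a stated assumption.

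**Step 1: chance imbalance in mean TBSA.** SE of the difference = SD × √(2/45) = SD × 0.211.

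| Assumed TBSA distribution | SD | SE (points) | 95% range (1.96 × SE) | As % of mean |
|---|---|---|---|---|
| Uniform on 1–30%, mean 15.5 | 29/√12 = 8.37 | 1.76 | ±3.5 | 22% |
| Skewed, mean 8 | 6 | 1.26 | ±2.5 | 31% |
| Skewed, mean 6 | 5 | 1.05 | ±2.1 | 34% |

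A chance difference of 2 to 3.5 points is thus plausible at this sample size.

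**Step 2: gain from adjustment.** If TBSA explains a share R² of the within-arm cost variance, adjustment multiplies the SE by √(1 − R²), which is worth a sample of 90/(1 − R²). For the interval widths, assume a cost coefficient of variation (CV) of 1.0. The raw 95% half-width is then 1.96 × 1.0 × √(2/45) = 41% of mean cost. The part of that due to TBSA is 41.3% × √R².

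| Assumed R² | SE multiplier | Equivalent N | Adjusted half-width | 95% range of the TBSA part |
|---|---|---|---|---|
| 0.1 | 0.95 | 100 | 39% | ±13% |
| 0.2 | 0.89 | about 112 | 37% | ±18% |
| 0.4 | 0.77 | 150 | 32% | ±26% |
| 0.6 | 0.63 | 225 | 26% | ±32% |

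With a CV of 0.8 or 1.2 the raw half-width is 33% or 50%; the SE multipliers do not change.

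**Step 3: simulation check with skewed costs.** 45 per arm, 4,000 runs per scenario. TBSA was uniform on 1–30%, or lognormal with median 6% limited to 1–30%. Expected cost was a constant plus a term proportional to TBSA, cut by 20% in one arm and multiplied by lognormal noise with log-SD 0.3, 0.6 or 0.9.

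- *Bias:* the raw and adjusted estimates both averaged between −0.195 and −0.201, against a true difference of about −0.20.
- *Power, small noise:* 0.34–0.55 raw, 0.84–0.89 adjusted.
- *Power, medium noise:* 0.20–0.27 raw, 0.29–0.33 adjusted.
- *Power, large noise:* about 0.12 raw, 0.13–0.15 adjusted.

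A second simulation with a different cost model (a constant, plus TBSA times lognormal noise, plus gamma noise) gave raw/adjusted SEs of 5.34/4.81, 2.92/2.31 and 1.92/1.17 at R² of 0.24, 0.40 and 0.62. The ratios are 0.90, 0.79 and 0.61, close to √(1 − R²) = 0.87, 0.77 and 0.62.

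**The case against.** The strongest reply is that this is a condensed article. It defines what is divided by what, never uses the word unadjusted, and a regression-based difference in mean costs would still fit its wording. A fuller economic plan might specify one. That is possible. However, the article does state a cost contrast, names no covariate for it, gives a sensitivity analysis that leaves it unchanged, and confines planned adjustment to the primary outcome. On its face the estimator is the plain difference, and a better one is available from data already listed.

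Other parts of the objection stand and limit the point:

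- **No bias.** Randomization makes the raw difference unbiased, as step 3 shows. Nothing would be estimated wrongly.
- **Burn size need not act equally in both arms.** Every burn receives the allocated product, and Interventions gives the arms different dressing frequencies, so cost per % TBSA may itself depend on arm. For the same reason, setting whole-patient cost against a study-area outcome is not in itself an error; whole-patient costing also suits the societal perspective.
- **Timing of covariates.** Depth is determined on day 2–5 by clinical evaluation and laser Doppler scan, after randomization, and the text places a wound-size estimate after that step. Full thickness status at admission is not listed by name, only type of wound.

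A reader might infer that burn-size differences swamp the treatment effect, that adjustment would remove them, or that the cost comparison will be uninformative without it. The article supports none of these. It has no expected cost difference to set against the noise. Adjustment takes out only the share of variance that TBSA explains. And at low R² the adjusted interval is nearly as wide as the raw one (39% against 41% of mean cost at R² = 0.1).

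**Conclusion.** The point holds as a matter of efficiency. The stated cost contrast is unbiased but less precise than the planned data allow, because a baseline variable likely to predict whole-patient cost is left out and is not a stratification factor. The SE would be multiplied by about 0.89, 0.77 or 0.63 if TBSA explained 20%, 40% or 60% of cost variance. Those R² values are assumptions, as is the CV behind the interval widths. If depth, surgery, length of stay and productivity loss vary mostly for other reasons, the gain is small. It merits a change because it costs almost nothing and keeps the same target, the mean cost difference in the trial population.

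**What to change.** Specify the following in the analysis plan before costs are compared by arm:

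1. Estimate the mean cost difference from a regression of total cost on arm, center, TBSA% as recorded at admission, and age. Use a linear model, or a gamma model with average predicted costs per arm so that the result stays on the cost scale.
2. Take confidence intervals from a patient-level bootstrap.
3. Use this difference in the economic evaluation, including the dressing-change sensitivity analysis, and show the raw difference beside it.
4. Include full thickness status only if it was recorded at admission before randomization. Do not use the size or depth from the day 2–5 scan.

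The cost is a few lines of analysis-plan text and no new data. One check is needed: that the TBSA% used is the admission value. The eligibility limits of 1% and 30% are checked before randomization, so an estimate must have been made by then; confirm that it was kept.

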### Ethical consideration and safety

This study has been approved by the Medical Research Ethics Committee of Noord-Holland (NL43671.094.13). EudraCt number: 2013-000901-21. This study is also registered in the Netherlands Trial Registry (NTR), trial number 4486 and will be conducted in agreement with the Declaration of Helsinki, version Fortaleza (Brazil), October 2013, concerning the Ethical Principles for Medical Research Involving Human Subjects, and in accordance with the International Conference on Harmonization (ICH) of Good Clinical Practice (GCP) Guidelines and the valid Dutch laws. Adverse events (AEs), serious adverse events (SAEs) and suspected unexpected serious adverse reactions (SUSARs) are documented and reported to the competent authorities. All AEs will be followed until they have abated, or until a stable situation has been reached. Depending on the event, follow-up may require additional tests or medical procedures as indicated, and/or referral to the general physician or a medical specialist. There is no additional risk or discomfort for the patients in this study compared to daily practice. Since most of the measurements and questionnaires used in the study are also implemented in daily care of burn patients in the Dutch burn centers, participation does not involve a large extra burden for them.

## Discussion

This randomized controlled study will enable a comparison of the effectiveness, cost-effectiveness and quality of life of Flaminal**®** and Flamazine**®**, two common treatment modalities for partial thickness burns.

An accurate diagnosis of the partial thickness burns is essential in our study. Several studies have shown that clinical evaluation of burn depth is highly dependent on the experience of the clinician and that experienced clinicians are accurate in about 50–75 % of the cases [45–49]. Therefore, we use LDI, which has an accuracy of 95 % in combination with clinical evaluation of the wound, for measuring burn depth [49–51]. Furthermore, in our study two experienced wound specialists must agree on the time to complete re-epithelialization in order to optimize the accuracy of wound re-epithelialization. Bloemen et al. have shown that experienced observers are able to evaluate the re-epithelialization rate in a reliable and effective way [52]. No digital analysis is required to evaluate wound re-epithelialization since clinical evaluation by an experienced burn specialist is as equally effective as digital analysis [53].

This study will contribute to optimize the treatment of patients with partial thickness burn wounds from both the clinical and economical perspective.

### Trial status

Recruitment started in February 2014, and was completed on 20 October 2015. The follow-up of included patients is ongoing. The planned end date of the data collection is November 2016.

## Abbreviations

GCP: Good Clinical Practice
GLG: glucose oxidase combined with lactoperoxidase, stabilized by guaiacol
METC: Medical Research Ethics Committee (MREC); in Dutch: medisch ethische toetsing commissie (METC)
PBD: post-burn day
PEG: hydrated alginates polymers in a polyethyleneglycol
POSAS: Patient and Observer Scar Assessment Score
RCT: randomized controlled trial
SSD: silver sulphadiazine
TBSA: total body surface area
